### Data analysis

Calculations will be conducted according to incident patients (especially for mortality, where each patient cannot count for several exposures), and episodes (for example, regarding treatment impact, where several exposures of the same patient are potentially informative).

Continuous variables will be presented as mean and standard deviation in case of a normal distribution and as median and interquartile range with variables without normal distribution.

Interval-scaled and ordinal-scaled variables will be presented as median and interquartile range.

Categorical variables will be presented as frequency and percentages.

For continuous variables, comparisons between outcome categories will be analyzed using parametric tests for normally distributed variables and non-parametric tests for non-normally distributed variables. For categorical variables, comparisons will be performed using the Pearson’s Chi-squared test or Fisher’s exact test. Multivariable approaches will assess significance of variables of interest after multivariable analyses. Statistical analyses will be performed using the latest version of R (R Core Team).

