Further investigation is needed to determine the optimal EEG target in patients with RSE and SRSE. Commonly used EEG surrogates of RSE control include seizure suppression, the emergence of a burst-suppression pattern (BS), or an isoelectric background. Achieving these surrogate endpoints often requires titrating intravenous antiepileptic drugs based on EEG readings. A multinational survey favored BS as the preferred target for CIVAD titration in RSE patients [43], with an interburst interval of around 10 s suggested by experts [44]. Achieving BS could be challenging and was not associated with sustained seizure termination or better outcome in a recent observational study [45]. The adequacy of BS as a surrogate target then lacks substantial evidence [46].

Finally, although the treatment of CSE is well established, these recommendations are often extrapolated to NCSE due to lack of data confirming the appropriateness of this practice. Currently, there is no clear consensus on the treatment of NCSE.

To address all these issues, randomized and controlled trials are needed. Such trials require substantial financial and human resources to achieve sufficient statistical power [47]. This is a challenge for RSE and SRSE, which have a low annual incidence of respectively up to 7 per 100.000 adults and 1 per 100.000 adults [48–50]. Other limitations include the challenges of clinical trials in the emergency setting and in temporarily incapacitated subjects.

Multicenter prospective observational registries offer an alternative approach to randomized controlled trials by collecting data on determinants of outcome, practice variability and allow comparative effectiveness and efficacy studies. Recently, the Sustained Effort Network for treatment of Status Epilepticus (SENSE) has provided real-life data about SE [51–55]. Between January 2011 and June 2015, 1179 episodes of SE in 1049 subjects from eight German-speaking centers in Austria, Germany, and Switzerland, were enrolled in SENSE. Collected data helped provide new insights into the factors contributing to SE cessation and refractoriness, functional outcome, and intubation.

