### Management protocol

No common management protocol will be imposed on the participating centers. However, most institutions have established a local protocol that is closely related to the most recent guidelines for the management of SE published by the American Epilepsy Society (AES) in 2016 [64].

In general, diagnosis of SE and related conditions is made based on clinical suspicion using physical examination and, where necessary, EEG (including, cEEG).

In most cases, emergency cerebral imaging with CT or MRI as well as standard emergency blood analysis, and CSF analysis if indicated, will be performed. Most frequently, the first treatment step consists of the administration of a benzodiazepine. If unsuccessful, intravenous administration of ASMs such as levetiracetam, valproate, (fos-)phenytoin, or lacosamide follows. As a third step, another ASM is added or anesthetics such as propofol or midazolam. All treatment decisions will remain at the discretion of the attending physicians.

The use of data acquisition sheets for the very early stages SE (Annex; modified from [56]) and ASM trials for IIC, which are already in place in some centers, will be encouraged to facilitate homogenous and complete data collection.

All participating centers perform cEEG for the following indications:

Management of refractory and super-refractory SE.Suspicion of NCSE after a convulsive SE or seizure (lack of return to neurological baseline).

Some participating perform cEEG for additional indications, such as patients unexplained altered mental status, detection of delayed cerebral ischemia in aneurysmal, subarachnoid hemorrhage.

The availability of cEEG is specific to each center, varying from 7 days a week (including Sundays and holidays) to during working hours on weekdays.

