### Data security and quality assessment

Recorded data are pseudonymized using site-specific sequential alphanumeric codes known to the local investigators only. Data entry is compliant with General Data Protection Regulation (GDPR) 2016/679 of European Union law. In countries where more restrict data protection rules are in place, only anonymized data will be provided.

Data collection will be performed using Research Electronic Data Capture (REDCap) electronic data capture tools hosted at Erasme Hospital [65, 66] REDCap is a secure, web-based software platform designed to support data capture for research studies, providing (1) an intuitive interface for validated data capture, (2) audit trails for tracking data manipulation and export procedures, (3) automated export procedures for seamless data downloads to common statistical packages, and (4) procedures for data integration and interoperability with external sources. Data are collected prospectively from the admission of the patient to discharge. Documentation must be started latest at the third working day after treatment to guarantee data quality. In some centers, data collection will be not feasible for a limited number of weeks for organizational reasons. These times will be communicated in advance to the steering committee. However, in the other time the consecutive inclusion of patients will be guaranteed.

Center participation will be monitored by a study coordinator to ensure consecutive case assessment and timely data entry. An independent data monitoring committee will periodically review data entry for completeness and accuracy. Any query due to missing data or lack of consistency will be resolved with local investigators.

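### Treatment impact is analysed per episode, with some patients counted more than once, but the only tests named assume independent observations and no allowance for patient or centre correlation is stated

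*Protocol article*

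**What the plan says.** The Data analysis section of the protocol article sets two units of calculation. One is the incident patient, "especially for mortality, where each patient cannot count for several exposures". The other is "episodes (for example, regarding treatment impact, where several exposures of the same patient are potentially informative".

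It then names tests. Measurements on a continuous scale are covered by this statement: "comparisons between outcome categories will be analyzed using parametric tests for normally distributed variables and non-parametric tests for non-normally distributed variables". Categorical data get a separate rule, which reads: "For categorical variables, comparisons will be performed using the Pearson’s Chi-squared test or Fisher’s exact test". A further sentence refers to multivariable analysis without naming a model. The article mentions no random effect, generalised estimating equation, robust variance or centre term.

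Other sections bear on whether observations are independent:

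- Background: the predecessor registry enrolled "1179 episodes of SE in 1049 subjects from eight German-speaking centers".
- Management protocol: "No common management protocol will be imposed on the participating centers". The same section says that access to continuous EEG ranges from every day of the week to weekday working hours, depending on the centre.
- Objectives: whether care and outcome differ between centres is itself a study question.
- Data security and quality assessment: in countries with stricter rules, "only anonymized data will be provided".

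**The concern.** The unit and the tests do not fit together. A drug is a categorical variable and cessation of status epilepticus is an outcome category, so comparing them over episodes falls naturally under the chi-squared or Fisher sentence. Those tests treat two episodes of one patient as two unrelated people. The authors saw the issue for mortality, where they count each patient once, but state no adjustment where they keep the repeats.

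The same applies to centres. The Background lists third-line treatment and the use of continuous EEG as comparative-effectiveness targets, and both may follow local practice. If outcomes also differ by centre, a pooled comparison without a centre term has two problems. Its standard error can be too small, and its estimate may mix the centre effect with the treatment effect.

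At stake is the calibration of p-values and intervals for the comparisons meant to guide decisions and future trials.

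**Working it through.** **Plan's own figure.** There is none for clustering. The Sample size section counts patients (3000, of whom 1500 refractory and about 150 super-refractory) without a design effect.

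**Inputs from the article.** 1179 episodes, 1049 subjects, 12 centres, 3000 and 1500 patients. All intraclass correlations (ICC) below are assumptions, because the article gives none.

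**Formulas.** Design effect DE = 1 + (m − 1) × ICC of outcome × ICC of exposure, with m the size-weighted mean cluster size, Σm²/Σm. True level of a nominal 5% two-sided test = 2 × [1 − Φ(1.96/√DE)].

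**Repeat episodes.** 1179 − 1049 = 130 repeat episodes, which is 130/1179 = 11.0%. If each repeater has two episodes, 130 patients have two and 919 have one, so m = (919 + 130 × 4)/1179 = 1.221. With exposure constant within patient (exposure ICC 1):

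| Patient ICC | DE | True level |
|---|---|---|
| 0.1 | 1.022 | 5.3% |
| 0.3 | 1.066 | 5.8% |
| 0.5 | 1.110 | 6.3% |
| 1 | 1.221 | 7.6% |

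Sensitivity:

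- If repeaters have five episodes each, m = 1.551. At patient ICC 0.5, DE is 1.28 and the level 8.3%.
- If exposure is unrelated between a patient's episodes, DE is 1.00.
- If exposure always switches (exposure ICC −1, patient ICC 0.5), DE = 1 − 0.221 × 0.5 = 0.89 and the level is 3.8%, so the test is conservative.

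**Centres.** Equal sizes are assumed: 3000/12 = 250 for the whole cohort and 1500/12 = 125 for the refractory group.

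| Outcome ICC | Exposure ICC | DE, m = 250 | Level | DE, m = 125 | Level |
|---|---|---|---|---|---|
| any | 0 | 1.00 | 5.0% | 1.00 | 5.0% |
| 0.01 | 0.1 | 1.25 | 7.9% | 1.12 | 6.4% |
| 0.02 | 0.1 | 1.50 | 10.9% | 1.25 | 7.9% |
| 0.02 | 0.3 | 2.49 | 21.5% | 1.74 | 13.8% |
| 0.05 | 0.3 | 4.74 | 36.8% | 2.86 | 24.6% |

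For example, 1 + 249 × 0.02 × 0.1 = 1.50. In the super-refractory group (150/12 = 12.5 per centre) the last row gives only DE 1.17 and a level of 7.0%. These levels cover precision only. Confounding by centre would come on top and cannot be sized from the article.

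**The case against.** The strongest reply is that this is a condensed article. Its multivariable model is unnamed and could already be a mixed, GEE or robust-variance model, set out in a fuller protocol or analysis plan that is not shown. The named tests are also attached to comparisons between outcome categories, not expressly to the episode-level treatment analysis. This stands in part: the article does not show that every treatment result will be too optimistic. It does not remove the point, because the article states both the unit and the tests, and an adjusted model would not repair the unadjusted tests.

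Three stronger readings are tempting and are not supported:

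- *Error rates of 19-42%.* With outcome ICC 0.01-0.02 these follow only if exposure is fixed wholly by centre (exposure ICC 1; for example 1 + 249 × 0.02 = 5.98, level 42%). For drug choice the Management protocol section points the other way. It leaves treatment decisions to the treating physicians, and says most local protocols stay close to one guideline. Even for continuous EEG, all centres share two core indications.
- *Centre differences will be read as drug effects.* They may be, but the article makes centre differences a study question and plans multivariable analysis.
- *Mortality will be miscounted where data are anonymised.* Nothing says that no patient index is kept, and one count per patient is already planned. A patient dies once, so unlinked repeats would enlarge the denominator. On predecessor figures, mortality would be understated by at most about 11% (1049/1179 = 0.89), at affected sites only.

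**Conclusion.** The point holds as a stated mismatch between the unit of analysis and the named tests. The part due to repeat episodes is modest: about 5.3-7.6% instead of 5%, given the predecessor's repeat rate, two episodes per repeater, patient ICC 0.1-1 and constant exposure. It vanishes or reverses if exposure varies within a patient.

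The centre part is potentially larger but applies only to exposures that follow centre, notably continuous EEG. Over 12 × 250 patients it runs from no effect, through about 11% (outcome ICC 0.02, exposure ICC 0.1), to about 37% (0.05 and 0.3). Which of these applies cannot be told from the article. The correction is worth making before analysis; the figures do not show that the registry's results will be invalid. The anonymisation issue is a conditional safeguard, not an established defect.

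**What to change.** 1. For every episode-level or exposure-level comparison, replace the independence tests by a mixed-effects or GEE model, or by cluster-robust variance, with patient as cluster and centre as a fixed or random effect. If variance is clustered on the 12 centres, use a small-cluster correction. Resampling by patient alone would leave centre clustering untouched.
2. Add a sensitivity analysis restricted to each patient's first episode. Keep the planned single count per patient for mortality.
3. Confirm that sites delivering anonymised data keep a non-identifying patient index and an episode number, so that the patient-level mortality analysis can be done there. This should be settled during collection, as it may not be recoverable later.

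The cost is a change of analysis wording, at most two non-identifying fields, and somewhat wider intervals. With fixed centre effects, an exposure that varied only between centres could not be estimated, so such a comparison would need a random centre effect and would rest on about 12 units.

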## Discussion

SENSE allowed to include over 1000 patients with SE from 8 centers. The study provided real-life data about SE and in particular refractory SE [54, 55].

It confirmed that a large proportion of first-line treatments was underdosed compared to the guidelines [54]. First-line treatment did not include benzodiazepines in 20% of all cases, 6% and 22% in CSE and non-CSE, respectively. These findings strongly suggest that IV ASMs are less efficacious than benzodiazepines as first-line treatment. Several predictors of SE cessation have been identified, such as a younger age, a lower mRS before SE onset, lower number of comorbidities, benzodiazepine as first-line treatment and a higher cumulative dose of ASMs within the first 30 min [53, 54]. Refractoriness occurred in 55% of patients and was associated with a higher baseline mRS and treatment deviation from guidelines, such as a lower bolus dose than recommended [54]. Unlike other studies, no difference was found comparing etiologies of refractory and non-refractory SE. Variables associated with good outcome in RSE were lower SE Severity Score (STESS) at SE onset, a shorter SE duration, a shorter length of stay and a lack of intubation. More than 70% of refractory SE were treated without airways protection and or mechanical ventilation. Limitations mentioned by the authors were the variability in recruitment of patients through the different centers, who could decrease the cohort homogeneity and potentially impacting on generalizability. Continuous EEGs were not available for most patients, even though it was recommended by several scientific societies [64, 68]. The focus of SENSE was RSE but only a few SRSE were recruited.

SENSE-II/AROUSE will provide high-quality data on SE of all types and severities. We have planned to collect continuous EEG data, if applicable, to alleviate the lack of knowledge about electrographic patterns of NCSE. We will focus on the functional outcome of SE but also on the refractoriness and super-refractoriness to identify potential predictors. Finally, due to lack of studies of third-line treatment and beyond, we plan to perform a comparative effectiveness study based on the collected data.

The evaluation of a large, heterogeneous patient group will hopefully help in clinical decision making in an area where data with higher level of evidence are still lacking.

## Data Availability

Not applicable.

## Abbreviations

ACNS: American Clinical Neurophysiological Society
AES: American Epilepsy Society
ASM: Anti-seizure medication
CIVADs: Continuous intravenous anesthetic drugs
CSE: Convulsive status epilepticus (i.e., bilateral tonic clonic)
CT: Computer tomography
EEG: Electroencephalogram
EMSE: Epidemiology-based mortality score in status epilepticus
ESETT: Established status epilepticus treatment trial
FDG: Fluorine-18 fluorodeoxyglucose
GDPR: General Data Protection Regulation
IC: Informed consent
ICC: Ictal-interictal continuum
ICU: Intensive care units
ILAE: International League Against Epilepsy
IV: Intravenous
MRI: Magnetic resonance imaging
mRS: Modified Rankin Scale
NCSE: Nonconvulsive status epilepticus
NORSE: New Onset Refractory Status Epilepticus
PET: Positron emission tomography
REDCap: Research Electronic Data Capture
RSE: Refractory status epilepticus
SE: Status epilepticus
SENSE: Sustained effort network for treatment of status epilepticus
SENSE-II/AROUSE: Sustained effort network for treatment of status epilepticus/European Academy of Neurology Registry on refractory Status Epilepticus
SRSE: Super refractory status epilepticus
STESS: Status epilepticus severity score
